## 7.6 Data Analysis

### 7.6.1 Analysis of the Primary Endpoints

Baseline descriptive statistics on all evaluable patients will be provided for demographic variables (age, sex, race/ethnicity), performance status, disease stage and status at the time of enrollment and treatment regimens previously used.

The NCI Common Terminology Criteria for Adverse Events, version 4 (CTCAE v4) will be used to evaluate toxicity. We will consider a toxicity to be an adverse event that is possibly, probably or definitely related to TRACT treatment. The maximum grade of toxicity for each category of interest will be recorded for each patient and the summary results will be tabulated by category and grade. We will describe all DLTs and other serious ( $\geq$  Grade 3) AEs on a patient-by-patient basis; descriptions will include dose level and any relevant baseline data. Data on the dose of cells they received will be tabulated.

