## SCHEDULE OF EVENTS: SAMPLE COLLECTION FOR TRACT STUDY

[figure not shown]

Escalating doses of autologous expanded Tregs (TRACT) will be administered to the next cohort of patients if there are no observed serious adverse events within 30 days of TRACT infusion as follows:

Tier 1:  $0.5 \times 10^9$  total expanded Tregs (n=3)

Tier 2:  $1 \times 10^9$  total expanded Tregs (n=3)

Tier 3:  $5 \times 10^9$  total expanded Tregs (n=3)

Tier 4:  $8 \times 10^9$  total expanded Tregs (n=3)

Patients will be monitored at various time points, as described above for evidence of donor-specific transplantation tolerance using in vitro analyses, specifically mixed-leucocyte reaction assays (MLR). Graft function will be monitored clinically in the standard fashion. The overall goal for this phase I study is to demonstrate the safety of TRACT administration in kidney transplant recipients, and lay the foundation for a subsequent phase 2 trial. If we are successful, this approach could have for a transformative effect upon the field of solid organ and cellular transplantation.

The clinical site for recruitment, enrollment, and treatment of patients will be Northwestern Memorial Hospital. The Principal Investigator is part of a team with the most active living donor renal transplant program in the nation, with more than 160 such transplants performed in 2011. There already exists a robust infrastructure for combined therapeutic cell transfer (stem cell) and solid organ transplantation with two protocols for living donor renal transplants + HSC having been active at Northwestern for almost 5 years; [name], the IND sponsor and co-investigator, serves as PI or co-PI on these trials (50, 51).

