#### **Serious Adverse Event**

Adverse events are classified as serious or non-serious. A *serious adverse event* is any AE that is:

- fatal
- life-threatening
- requires or prolongs hospital stay
- results in persistent or significant disability or incapacity
- a congenital anomaly or birth defect
- an important medical event

Important medical events are those that may not be immediately life threatening, but are clearly of major clinical significance. They may jeopardize the subject, and may require intervention to prevent one of the other serious outcomes noted above. For example, drug overdose or abuse, a seizure that did not result in in-patient hospitalization, or intensive treatment of bronchospasm in an emergency department would typically be considered serious.

**Unrelated** ---Any reaction that is clearly due to extraneous causes AND that is likely to have been produced by the subject's clinical state or other modes of therapy administered to the subject.

**Unlikely** ---Any reaction that does not follow a reasonable temporal sequence from the study intervention (in this case TRACT infusion) OR that is likely to have been produced by the subject's clinical state or other modes of therapy administered to the subject.

**Possible** ---A reaction that follows a reasonable temporal sequence from the study intervention (in this case infusion of TRACT) OR that follows a known response pattern to the suspected drug AND that could not be reasonably explained by the known characteristics of the subject's clinical state or other modes of therapy administered to the subject.

**Probable** ---A reaction that follows a reasonable temporal sequence from the study intervention (in this case TRACT infusion) OR that follows a known response pattern to the suspected drug AND that could not be reasonably explained by the known characteristics of the subject's

clinical state or other modes of therapy administered to the subject *AND* improves with the reduction in dose or cessation of the intervention.

**Definite**---A reaction that follows a reasonable temporal sequence from the study intervention (in this case TRACT infusion and toxicities occurring during the first 24 hours post-infusion) *AND* that follows a known response pattern to the suspected therapy

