#### **Pregnancy**

Any pregnancy which occurs during this study will be reported as an SAE for tracking purposes. All pregnancies which are identified during this study will be followed to conclusion and outcome reported. All pregnancies will be reported on a SAE form.

Female patients will be instructed to immediately inform the Investigator of any pregnancies. There is currently no data relating to the effects of Treg on a developing fetus or nursing baby. The sponsor/investigator will counsel the patient, discuss the risks of continuing with the pregnancy and the possible effects on the fetus. Monitoring of the patient will continue until the conclusion of the pregnancy.

All adverse events that do not meet any of the criteria for serious should be regarded as *non-*

*serious adverse events.*

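### Section 7.6.1 uses 'serious' to mean Grade 3 or higher while section 9.1 defines it by outcome, so the patient-by-patient safety description omits serious adverse events below Grade 3

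*Protocol*

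**What the plan says.** Protocol section 7.6.1 (Analysis of the Primary Endpoints) promises two adverse event outputs. The first tabulates, by category and grade, each patient's maximum grade of toxicity, where a toxicity is an event at least possibly related to the cell product. The second is individual: "We will describe all DLTs and other serious", followed by a parenthesis with a greater-than-or-equal sign that continues "Grade 3) AEs on a patient-by-patient basis; descriptions will include dose level and any relevant baseline data".

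Section 9.1 uses the same word differently. Under Serious Adverse Event it states that "Adverse events are classified as serious or non-serious" and lists outcomes: death, threat to life, hospital stay, lasting disability, birth defect, or an important medical event. The hospital criterion reads "requires or prolongs hospital stay". The last criterion is explained as follows: "Important medical events are those that may not be immediately life threatening, but are clearly of major clinical significance". No grade appears in the list. Under Pregnancy, "Any pregnancy which occurs during this study will be reported as an SAE for tracking purposes". The residual rule begins "All adverse events that do not meet any of the criteria for serious should be regarded as" and assigns all such events to the non-serious class. The subsection on hospitalization again makes an event that leads to a hospital stay an SAE, with exceptions for certain planned or target-disease stays and no mention of grade.

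**The concern.** Grade measures intensity and seriousness measures outcome. Section 9.1 keeps them apart, giving severity its own scale (mild, moderate, severe). Section 7.6.1 merges them in the sentence that fixes the individual safety description.

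This is a 12-patient phase I trial whose primary objective is safety, so the case-by-case description is a central product. If it follows the 7.6.1 wording, a reader of the final report could take it as complete for SAEs when it is not. The same reader could also take some events to be SAEs when under 9.1 they are not.

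**Working it through.** The protocol gives no figure on this point and no formula applies. The check is a cross-classification of events under the two definitions.

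Inputs:

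- Section 7.6.1: individual description covers DLTs plus serious events, with serious glossed as Grade 3 or higher.
- Section 9.1: serious is defined by outcome only; pregnancy is added; everything else is non-serious.
- Section 7.4: a DLT is a Grade 3 or 4 non-hematologic toxicity, with listed exceptions. Grade 3 or 4 toxicity during the infusion is also recorded as a DLT.
- Section 9.1, Abnormal Laboratory Values: laboratory abnormalities can be adverse events and so can carry a grade.

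| Event | Serious under 9.1 | Grade 3 or higher | Described under 7.6.1 |
|---|---|---|---|
| a | yes | yes | yes |
| b | yes | no, or ungraded | no |
| c | no | yes | yes, and called serious |
| d | no | no | no |

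**Row b, the omission.** The DLT limb does not bring these events back, because every DLT is Grade 3 or 4. Candidates are an important medical event of lower grade, a lower-grade event with a hospital stay, and a pregnancy, which need carry no toxicity grade. Fatal and, in practice, life-threatening events would be Grade 3 or higher, so they fall in row a.

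**Does the other output catch row b?** Only in part. The category-by-grade table covers toxicities, meaning events possibly, probably or definitely related to the product. A related Grade 1 or 2 SAE can enter that table, but without a seriousness flag. An SAE below Grade 3 judged unrelated or unlikely to be related enters neither output. Section 7.6.2 covers only kidney function and does not reach these events.

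**Row c, the label.** Section 7.4 itself foresees Grade 3 or 4 laboratory disturbances that respond to correction. Where such an abnormality is an adverse event and meets no 9.1 outcome, 7.6.1 calls it serious and 9.1 calls it non-serious.

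**Alternative reading of the parenthesis.** It could be a filter: serious events that are also Grade 3 or higher. Row b is then still omitted. The mislabelling in row c disappears, but row c events that are not DLTs are then not described at all. Naming DLTs, themselves Grade 3 or 4, alongside *other* serious events favours the definitional reading. The omission holds on both.

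**The case against.** The strongest reply is that nothing is lost. Every SAE under 9.1, whatever its grade, is recorded under 9.2 and reported within 24 hours with a written narrative under 9.3.1. SAEs are also discussed monthly under 8.1, and monitoring data are reviewed before each escalation under 9.4. Pregnancies are followed to their conclusion and the outcome is reported. All of this stands. A reader might infer that SAEs disappear from the trial; the documents do not support that. The gap lies in the analysis output.

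A reader might also infer that the two meanings could pass or fail the same cohort, because the general design says that escalating doses "will be administered to the next cohort of patients if there are no observed serious adverse events within 30 days of TRACT infusion". That sentence uses the term that 9.1 defines, and nothing shows that it takes over the grade gloss from an analysis section.

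It is tempting to size the problem from the infusional toxicity table in section 1.4, which shows five Grade 2 events and one Grade 3 event in 23 patients. With one event per patient, a tier of three would contain a Grade 3 event with probability 1 − (22/23)³ = 12%. If every Grade 2 event were also counted, the figure would be 1 − (17/23)³ = 60%. These are chances that an event occurs in a tier, not that an SAE is left out of 7.6.1. They come from a different population and cell source, and the table does not say which events met an outcome criterion.

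Two further cautions are fair. Whether an event that needs admission can stay below Grade 3 depends on CTCAE v4, which is cited but not reproduced; the protocol's separate severity scale mentions hospitalization only under severe. Nor is the individual description the only item in 7.6.1 that involves dose, since the cell dose received is also tabulated.

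Finally, listing details often belong in the statistical analysis plan. Here, however, the protocol states a rule that conflicts with its own definition, and a later plan would inherit it.

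**Conclusion.** The point holds as an inconsistency between the primary analysis and the protocol's own definition. As written, the individual description omits SAEs that are below Grade 3 or ungraded, and those judged unrelated are absent from both adverse event outputs of 7.6.1. On the definitional reading, events of Grade 3 or higher that meet no 9.1 criterion are also called serious.

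The conclusion assumes only that some SAEs can fall below Grade 3 or lack a grade. The important-medical-event and pregnancy provisions carry no grade requirement, so it does not depend on the hospital-stay example. The number of affected events cannot be estimated from the documents. No DLT, MTD or stopping decision changes, nor does any sample size or error rate. It is worth correcting because the safety description is a main product of the trial and the correction is easy.

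**What to change.** In section 7.6.1, replace the sentence with one that describes patient by patient, with dose level and relevant baseline data:

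1. all DLTs;
2. all SAEs as defined in section 9.1, regardless of grade or relatedness;
3. as a separate category not called serious, all other adverse events of Grade 3 or higher.

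The cost is one sentence and a slightly longer listing. Grade and seriousness are both already assessed, so no new data are needed. Laboratory events of Grade 3 or higher that count as adverse events stay in the listing; only their label changes.

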### **7.6.2 Analysis of Secondary Endpoints**

Clinical responses will be documented using the standard indicators of kidney function.

## **8 DATA SAFETY MONITORING PLAN**

### **8.1 Monitoring and Quality Assurance**

Investigator/Sub-investigators and clinical research staff meet monthly to review and discuss study data to include, but not limited to, the following:

- serious adverse events
- subject safety issues
- recruitment issues
- accrual
- protocol deviations
- breaches of confidentiality

All study participants on Phase I studies are also reviewed weekly for any toxicity or other untoward events. All toxicities encountered during the study will be evaluated on an ongoing basis according to the NCI Common Toxicity Criteria version 4.0 and recorded prior to each course of the investigational treatment. Any modifications necessary to ensure subject safety and decisions to continue or close the trial to accrual are also discussed during these meetings. All study data reviewed and discussed during these meetings will be kept confidential.

Any modifications necessary to ensure subject safety will be submitted to the IRB prior to implementation. The IRB will be notified of any change in the risk/benefit ratio which would affect whether the study should continue. All protocol deviations or breaches of confidentiality will be reported to the IRB according to IRB guidelines. If any literature becomes available which suggests that conducting this trial is no longer ethical the study will be terminated and the IRB will be notified of the new findings in the form of an Unanticipated Problem submission. All study treatment associated adverse events that are both serious and unexpected will be reported to the IRB according to the established guidelines.

All records related to this research study will be stored in a locked environment. Only the researchers listed on the first page of this form and their staff will have access to the research records. Any breach in subject confidentiality will be reported to the IRB in the form of an Unanticipated Problem submission.

## 9 Safety and Adverse Events

### 9.1 Definitions

#### **Adverse Event**

An *adverse event* (AE) is any symptom, sign, illness or experience that develops or worsens in severity during the course of the study. Intercurrent illnesses or injuries should be regarded as adverse events. Abnormal results of diagnostic procedures are considered to be adverse events if the abnormality:

- results in study withdrawal
- is associated with a serious adverse event
- is associated with clinical signs or symptoms
- leads to additional treatment or to further diagnostic tests
- is considered by the investigator to be of clinical significance

#### **Serious Adverse Event**

Adverse events are classified as serious or non-serious. A *serious adverse event* is any AE that is:

- fatal
- life-threatening
- requires or prolongs hospital stay
- results in persistent or significant disability or incapacity
- a congenital anomaly or birth defect
- an important medical event

Important medical events are those that may not be immediately life threatening, but are clearly of major clinical significance. They may jeopardize the subject, and may require intervention to prevent one of the other serious outcomes noted above. For example, drug overdose or abuse, a seizure that did not result in in-patient hospitalization, or intensive treatment of bronchospasm in an emergency department would typically be considered serious.

**Unrelated** ---Any reaction that is clearly due to extraneous causes AND that is likely to have been produced by the subject's clinical state or other modes of therapy administered to the subject.

**Unlikely** ---Any reaction that does not follow a reasonable temporal sequence from the study intervention (in this case TRACT infusion) OR that is likely to have been produced by the subject's clinical state or other modes of therapy administered to the subject.

**Possible** ---A reaction that follows a reasonable temporal sequence from the study intervention (in this case infusion of TRACT) OR that follows a known response pattern to the suspected drug AND that could not be reasonably explained by the known characteristics of the subject's clinical state or other modes of therapy administered to the subject.

**Probable** ---A reaction that follows a reasonable temporal sequence from the study intervention (in this case TRACT infusion) OR that follows a known response pattern to the suspected drug AND that could not be reasonably explained by the known characteristics of the subject's

clinical state or other modes of therapy administered to the subject *AND* improves with the reduction in dose or cessation of the intervention.

**Definite**---A reaction that follows a reasonable temporal sequence from the study intervention (in this case TRACT infusion and toxicities occurring during the first 24 hours post-infusion) *AND* that follows a known response pattern to the suspected therapy

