### **6.6 Preparation and Administration of Study Drugs**

#### ***6.6.1 TRACT (Investigational Product)***

The TRACT cellular product that has been released following confirmation of release criteria compliance will be infused as a fresh, non-cryopreserved product, intravenously in the Northwestern Clinical Research Unit by the PI or his designee. TRACT is given only once at the designated dose level per subject during this study.

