A dose-limiting toxicity (DLT) is defined as a clinically significant adverse event or abnormal laboratory value assessed as unrelated to the kidney transplant, intercurrent illness, or concomitant medications and occurring during the first 3 weeks after administration of the first dose that meets any of the following criteria: grade 3 or 4 non-hematologic toxicity (except for electrolyte disturbances responsive to correction measures within 48h, diarrhea, nausea and vomiting that responds to standard medical care, rash  $\geq$  Grade 3 that response to supportive care, infusion relation reaction that are responsive to supportive care, infections and infectious complications related to patients neutropenia, elevated creatinine  $<3.5 \times$  upper limit of normal, elevated AST  $< 8 \times$  upper limit of normal, elevated ALT  $<8 \times$  upper limit of normal, elevated bilirubin  $< 5 \times$  upper limit of normal, elevated PTT  $< 3.5 \times$  upper limit of normal).

Dose escalation will only occur after patients, at a given dose level, have been followed for at least 21 days and no evidence of dose limiting toxicity has been seen. The dose level for a given patient and the progression of doses from one cohort of patients to the next will be adjusted based on adverse events. If a patient is discontinued due to concurrent illness unrelated to toxicity or organ rejection before they reach the end of the treatment cycle (21 days after the infusion), an additional patient will be enrolled at that same dose level.

| No. of Patients with DLT at a Given Dose Level | Escalation Decision Rule                                                                                                                                                                                                                                              |
|------------------------------------------------|-----------------------------------------------------------------------------------------------------------------------------------------------------------------------------------------------------------------------------------------------------------------------|
| 0 out of 3                                     | Enter patient(s) at the next dose level.                                                                                                                                                                                                                              |

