Once a cohort is filled, enrollment into the next dose level will only begin after all patients in that cohort have passed through the DLT observation period. At that point, the PI, IND Sponsor, IND Medical Monitor and study co-investigators will review toxicity reports and recommend whether or not it is safe to proceed to the next cohort.

After escalation has stopped, de-escalation will begin at one dose level below the maximum achieved during escalation. The action taken depends on the number of patients previously treated at a dose level. If 3 or fewer patients have previously been treated, 3 patients are added; if 6 patients have previously been treated, this level will be declared to be the MTD. The MTD is defined to be the highest dose level at which no more than 1 of 6 treated patients experiences a DLT.

Patients within a cohort need not be accrued or treated at the same time; thus, accrual at a dose level should stop as soon as 2 patients at a dose level have experienced DLT at that level. There will be no intra-patient dose escalation or de-escalation.

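### The section 9.1 definition of *possible*, which decides entry to the primary toxicity table, is ambiguous, and the causality scale around it does not suit a one-time infusion

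*Protocol*

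**What the plan says.** **What enters the table.** Section 7.6.1 (analysis of the primary endpoints) states: "We will consider a toxicity to be an adverse event that is possibly, probably or definitely related to TRACT treatment". The maximum grade per category and patient is then tabulated. The same section describes all dose-limiting toxicities (DLTs) and other grade 3 or higher events patient by patient, with dose level.

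**The scale (section 9.1, under the serious adverse event definitions).**
- *Unlikely*: the event "does not follow a reasonable temporal sequence from the study intervention (in this case TRACT infusion) OR that is likely to have been produced"; the sources named are clinical state and other therapy.
- *Possible*: the event follows a reasonable temporal sequence, "OR that follows a known response pattern to the suspected drug AND that could not be reasonably explained by the known characteristics"; the sources named are again clinical state and other therapy.
- *Probable*: the wording of *possible*, plus the condition that the event "improves with the reduction in dose or cessation of the intervention".
- *Definite*: a temporal sequence, qualified as "in this case TRACT infusion and toxicities occurring during the first 24 hours post-infusion", and a known response pattern. It has no condition about other explanations.

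**Exposure.** Section 6.6.1: "TRACT is given only once at the designated dose level per subject during this study". Section 7.4: "There will be no intra-patient dose escalation or de-escalation". Sections 7.4 and 7.5 do provide for stopping an infusion in progress for grade 3 or 4 toxicity.

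**DLTs.** Section 7.4 uses its own attribution test: the event must be "assessed as unrelated to the kidney transplant, intercurrent illness, or concomitant medications".

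**The concern.** The trial is open label and has no control arm, with three patients planned per tier. Subjects are infused about 60 days after transplantation, following alemtuzumab and while on sirolimus and mycophenolate. Many later events will have a plausible second explanation, such as infection, rejection or cytopenia. Whether such an event enters the graded summary depends on how the assessor reads one unbracketed sentence. Two assessors can apply section 9.1 faithfully and put the same event on opposite sides of the line. On the strict reading, the table leaves out the events for which attribution is hardest, so its counts, and any pattern across the four tiers, would partly reflect wording.

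The dechallenge clause and the 24-hour qualifier are a separate matter. They were written for a treatment that can be reduced or withdrawn, or for an acute reaction. After the infusion ends, *probable* is in practice out of reach, and after 24 hours so is *definite*.

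**Working it through.** No sample size or event count is involved, and the plan states no figure to reproduce. The check enumerates the definitions.

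**Inputs (section 9.1).** Five yes/no features of an event: T = reasonable temporal sequence; K = known response pattern; X = reasonably explained by clinical state or other therapy; D = improves on dose reduction or cessation; W = within 24 hours of infusion, possible only if T holds.

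Number of patterns: T absent gives 2 × 2 × 2 = 8 (K, X, D). T present gives 2 × 2 × 2 × 2 = 16 (K, X, D, W). Total 24.

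**Rules.**
- *Definite* = T and W and K, on both readings.
- Strict reading: *possible* = (T or K) and not X; *probable* = the same, and D.
- Loose reading: *possible* = T or (K and not X); *probable* = T or (K and not X and D).
- In the table (section 7.6.1) = *possible* or *probable* or *definite*.

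**Results.**

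| | Strict | Loose |
|---|---|---|
| Patterns entering the table | 12 of 24 | 18 of 24 |
| Patterns with T that are left out | 6 | 0 |
| Patterns entering only through *definite* | 2 | 0 |
| *Probable* but not *possible* | 0 | 0 |
| Membership changed by removing the dechallenge clause | 0 | 0 |

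Strict count: T with not X gives 8; K without T and not X gives 2; T, K, X and W enters only as *definite* and gives 2; 8 + 2 + 2 = 12. Loose count: all 16 with T, plus 2 with K, no T and not X, gives 18.

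**What drops out on the strict reading.** All six excluded patterns with T have X. Four are after 24 hours, which is every otherwise explainable event in that period, with or without a known pattern. Two are within 24 hours without a known pattern.

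**Role of the other two conditions.** Every *probable* event is already *possible*, so the dechallenge clause removes nothing. The 24-hour qualifier removes nothing that *possible* would admit. On the strict reading it only closes the one route around the exclusion clause: without it, the two late patterns with T, K and X would enter as *definite* (12 + 2 = 14). On the loose reading the total stays at 18. The source of the loss is the clause in *possible*.

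**Overlaps and gaps.**
- Loose reading: an event that follows the infusion and is likely due to other therapy is both *possible* and *unlikely*.
- Both readings: an event within 24 hours with a known pattern, likely due to other therapy, is both *definite* and *unlikely*. An event with a known pattern, no temporal sequence and no other explanation is both *possible* and *unlikely*.
- Strict reading: an event after 24 hours with a temporal sequence, explained elsewhere reasonably but not likely so, fits no category.

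**Which reading is more natural.** On the loose reading, temporal sequence alone would also satisfy *probable*, and the two grades would collapse for every temporally related event. Keeping them distinct favours the strict reading, but the text does not settle it.

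These are counts of logical patterns, not frequencies of events.

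**The case against.** The strongest reply is that little is lost. Three parts of it stand.

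- Acute known-pattern infusion reactions, which belong to the 24-hour part of the primary safety endpoint (section 4.2), can be rated *definite* even when otherwise explainable. *Probable* can be used when an infusion is stopped. The scale therefore does work for those events.
- The events of most interest are captured without an attribution test. Section 4.2 monitors rejection, allosensitization and opportunistic infection for 30 days; section 3.3 makes infections a secondary objective; section 7.3.3 requires biopsy confirmation of rejection; section 9.2 records all adverse events; and section 7.6.1 describes grade 3 or higher events individually.
- DLTs have their own wording in section 7.4, so the section 9.1 scale does not drive escalation. A stricter bar for DLTs than for tabulated toxicities is not in itself a contradiction.

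A reader might go further and infer that the scale cannot work at all, that most events relevant to TRACT are screened out, or that 29 of the 30 monitored days are closed to counting. The documents do not support this. The 29 days concern which labels are available, not counts lost, since *possible* stays open throughout. There are no event rates from which a share could be derived.

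It can also be said that an all-causality table is a matter for the SAP, which is not shown. That is fair for table layout. It does not answer the definition of toxicity, which the protocol itself fixes in 7.6.1 and 9.1.

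**Conclusion.** The point holds in a limited form. The definition that decides entry to the graded toxicity summary admits two readings. On the more natural one, every otherwise explainable event after 24 hours is left out (four of the six excluded patterns with a temporal sequence). On the other, the same event can be counted and not counted at once. The categories overlap on both readings. The dechallenge and 24-hour conditions are ill suited to a single infusion, but given the pooling in 7.6.1 they are labelling faults.

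The effect is confined to the summary by category and grade, mainly grade 1-2 and later events. Its size in patients or events cannot be computed from the documents. The conclusion assumes that assessors apply section 9.1 as written and that the parenthesis in *definite* is a condition and not an illustration. It should be corrected, but it does not undermine the escalation decisions.

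**What to change.** 1. Section 9.1: bracket the OR and AND, and let *possible* cover an event that could be due to TRACT or to another cause. Make the five categories mutually exclusive and leave no gap between *possible* and *unlikely*.
2. Section 9.1: remove the dechallenge condition from *probable* and the 24-hour qualifier from *definite*, as neither suits a single infusion.
3. Section 7.6.1: tabulate all adverse events from the start of infusion by tier and maximum grade regardless of attribution, and show the related subset as supportive.
4. Section 7.4: state how its attribution wording relates to the section 9.1 scale, so that a reader can see why an event may be a tabulated toxicity and not a DLT.

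The cost is revised wording and one more table. Toxicity counts will look less favourable, because background events of transplantation and immunosuppression will appear in the main table.
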